#### Strategies to improve adherence to interventions {11c}

Individual interviews at the beginning of the MBCT treatment phase will serve to reinforce the rationale of the research, highlight the importance of practice and address potential barriers to engagement. Participants allocated to continue with treatment as usual will take part in an interview that will serve to reinforce their understanding of the importance of their contribution to the research and prevent tendencies towards ‘resentful demoralisation’. We will offer support to help patients to familiarise themselves with the technical aspects of videoconferencing.

#### Relevant concomitant care permitted or prohibited during the trial {11d}

Patients who are currently taking antidepressant medication will be eligible for the trial and medication use will be documented for statistical analysis. All patients will be encouraged to continue treatments as usual.

#### Provisions for post-trial care {30}

Patients’ GP and referring IAPT service will be informed of trial participation and the end of trial participation in writing.

### Outcomes {12}

#### Primary outcome

The primary clinical outcome will be reductions in depression symptomatology as assessed using the PHQ-9 [20]. The primary timepoint for outcome measures will be 34 weeks post-randomisation. Hence, the primary outcome will be PHQ-9 scores at 34-week follow-up (consistent with end-of-treatment monitoring in IAPT). The PHQ-9 is a widely used self-report measure of depression that represents an integral part of the management of depression in the IAPT pathway and has good psychometric properties.

#### Secondary outcomes

Secondary outcomes include PHQ-9 measured at 10 weeks post-randomisation, and other clinical outcomes measured at 10-week and 34-week follow-up. The authors report a test–retest reliability of 0.84 over a period of 48 h [20]. Other clinical secondary outcome measures will include the Generalized Anxiety Disorder Questionnaire (GAD-7) [24], the Phobia Scale and the Work and Social Adjustment Scale, all from the IAPT minimum data set (IAPT Toolkit, 2008/9), along with the Warwick-Edinburgh Mental Wellbeing Scale (WEMWBS) [25], Experiences Questionnaire (EQ) Decentering Scale [26] and Five Factor Mindfulness Questionnaire (FFMQ) [27]. A series of binarised outcomes will be derived, based on PHQ-9 and/or GAD-7. Recovery, reliable recovery, and reliable improvement will be reported using (i) PHQ-9 only to align with depression research literature and (ii) both PHQ-9 and GAD-7, to align with IAPT practice. We will also report deterioration and reliable deterioration with regard to PHQ-9 and GAD-7 separately. We will also track symptoms weekly using the PHQ-9, GAD-7, Phobia Scale and the Work and Social Adjustment Scale.

#### Baseline survey

Participant characteristics assessed as part of the MINI interview will allow us to make comparisons between eligible patients who declined to participate, and those patients who participated in the trial.

#### Economic evaluation

The economic evaluation will take a health and social care perspective, as required for evidence presented to NICE. In addition, the cost perspective will be broadened to include the costs of time off productivity losses, since these are known to be relevant and important in those attending IAPT services [28].

Costs will be calculated by collecting service use information using the Adult Service Use Schedule (AD-SUS), a self-report measure developed by the team at King’s College and used in previous trials of MBCT [19], modified for use online, to which routine unit costs will be applied [29]. We will collect data on all service use not just use related to mental health conditions, because there is evidence that successful treatment in IAPT can reduce use of all healthcare services [30]. In addition, comparison via randomised groups will ensure that any differences in cost are due to the impact of the MBCT intervention. Information on TAU will be collected via the AD-SUS, modified to ensure that all relevant services are included. Data on the use of the MBCT intervention will be collected via therapist records and costs estimated using the standard approach set out by Curtis [29], acknowledging the challenges of costing group-based interventions [31]. Outcomes for the economic evaluation will be QALYs, calculated using health utilities derived from the EQ-5D-5L [32, 33]. Costs and outcomes will be combined first in a cost-utility analysis using QALYS and second in a cost-effectiveness analysis using the PHQ-9, providing information on whether or not MBCT is worthwhile in terms of cost savings elsewhere or improvements in outcomes, and information will be provided to decision makers with statistical analysis of differences in costs, cost-effectiveness planes and cost-effectiveness acceptability curves [34].

#### Qualitative analyses

Qualitative analyses will be used to explore patient experience of the intervention and to understand how the treatment might best benefit patients in the IAPT pathway. Previous trials have shown considerable variation in the degree to which patients engage in mindfulness practice [13] and a major focus of the qualitative analyses will therefore be on factors influencing such engagement and its relation with dynamics of change. For this purpose, we will investigate the following: (1) patients’ views on acceptability of MBCT and mindfulness practice, and the experience of participating in the course remotely; (2) patients’ views of the changes they experience and their utilisation of mindfulness skills; and (3) patients’ views of the broader impact of MBCT on their lives.

A subsample of participants in the MBCT arm, estimated to be 24 (or until data saturation has been reached), will be invited to a qualitative telephone interview conducted by trained research assistants. Recruitment will be purposive, including patients across all sites, and seeking to achieve maximum variation in relation to (1) completion/non-completion of treatment, (2) response/non-response to treatment and (3) recruitment site (to examine contextual factors).

Written feedback provided in the protocol sheets that MBCT participants receive on a weekly basis will be used to inform subsampling and will also provide us with the opportunity to explore any unanticipated experiences and effects in more depth. In collaboration with service users, we will develop, and pilot test, a semi-structured topic guide based on the above aims. Interviews will be video-recorded, transcribed verbatim, and anonymised. Thematic analysis of interview transcripts will be conducted using a Framework approach [35], involving the coding and sorting of textual units according to both deductive and inductively derived categories, and the use of matrices to review the coded data, investigate commonalities and differences and search for patterns. Coding and data management will be facilitated by NVivo software.

Given that MBCT was originally developed for relapse prevention in patients who are in remission and its use for currently depressed treatment non-responders will require adaptations in how the manualised approach is delivered and made accessible for patients, we will also conduct qualitative interviews with the therapists involved in the trial. These will serve to investigate (1) the overall experience of the therapist, (2) their experience of supporting participants in their practice, (3) helpful and unhelpful aspects of MBCT for treatment non-responders and (4) therapists’ experience of its overall effectiveness. Interviews will be guided by a semi-structured topic guide and data processed using the same approach that will be applied to participants’ interviews (see above).

### Participant timeline {13}

Interested participants will undergo screening using a brief structured telephone interview conducted by the research assistant. Potential participants will be invited for an initial assessment session to be conducted via videoconferencing to ascertain eligibility using structured clinical interviews conducted by the research assistant and assess baseline levels of symptoms (baseline assessment). Eligibility interviews will be conducted as soon as possible after the screening. Baseline questionnaire assessments will be conducted within a window of 3 weeks before randomisation. Participants will be randomly allocated and learn about group assignment at least a week preceding the pre-intervention interviews held with both groups. After the 9-week treatment delivery period, participants will be assessed again at 10 weeks and 34 weeks post-randomisation. Patients will be asked to complete the follow-up assessments within a 1-week window and prompted weekly using phone, text, or email for up to four weeks, if not responsive. Patients are free to receive their usual care through the NHS while they wait to start MBCT. See Fig. 1 for a schematic diagram depicting the schedule of enrolment, interventions and assessments.

**Fig. 1 Fig1:**
[figure not shown]
Schedule of enrolment, interventions and assessments (displayed according to Standard Protocol Items: Recommendations for Interventional Trials [SPIRIT] template)

### Sample size {14}

Following previous suggestions for defining successful treatment outcome in depression [36], the study will be powered to enable detection of a Minimal Clinically Important Difference (MCID) [37]. Using a criterion of one standard error of measurement (38), the MCID for our primary outcome measure (PHQ-9) has been estimated to range from 2.59 under best-case reliability scenarios to 4.78 under worst-case reliability scenarios [38]. In order to detect an MCID at the smaller end of this range (2.59) using a standard deviation of 5.4 (as reported for the baseline data in the clinical trial that served to estimate the above-listed range of MCIDs in [39]), with 90% power at an alpha level of 0.05, 186 participants are required. In our previous large-scale multi-centre trial of MBCT for patients with a history of recurrent suicidal depression, 93% of participants provided follow-up data over a 1-year follow-up period [18]. Considering a rate of attrition of 20%, conservatively estimated to be above that observed in our previous research, we will recruit a total sample of 234 participants (117 in each arm, 78 per site). As currently available research suggests that trials using remote delivery generally show comparable or even lower rates of attrition, we would expect this estimate to be transferable to the use of videoconferencing delivery [40]. The research team will monitor attrition at regular milestones during the trial (e.g. at the point where 50% of participants have reached their scheduled 6-month follow-up time) and consider remedial steps to increase sample size, if this is needed. We have not inflated the sample size to take account of clustering within treatment groups, as reanalyses of previous trials of MBCT have found intra-class correlations (ICCs) for primary outcomes to be negligible [41].

### Recruitment {15}

Participating IAPT services will identify patients who are coming to the end of their high-intensity treatment and have not responded (PHQ-9 ≥ 10) or patients who within a 6-month window following the end of high-intensity therapy show levels of symptoms above caseness without prior remission. Data from the IAPT services originally listed as collaborators in our grant proposal indicated that we would be recruiting from a pool of more than 7500 non-responders per year. Remote delivery of the intervention will allow us to reach an even wider potential pool of participants and allow inclusion of further IAPT services given that participation in the treatment will not be restricted to people within the geographical regions of the sites. The research team will include further IAPT services as patient identification centres (PIC) to work together with the three research sites. As IAPT services can differ widely in their characteristics and organisational features of IAPT services have been shown to explain considerable variance in their outcomes (Clark et al., 2018), we will only include services that can provide a considerable number of participants and make sure that collaborating services do not show outlier characteristics. As a general rule, services included as PIC sites will have to have recovery rates above 45% and their percentage of IAPT therapists should be at least 40%. A short participant information sheet together with a ‘Permission for Researcher to Contact Form’ will be sent to potential participants either via email or post (in the latter case together with a stamped addressed envelope for their response) through the service. Potential participants will be invited to either contact the research team directly or send the completed ‘Permission for Researcher to Contact Form’ so that the researchers can contact the potential participant. If potential participants do not return the form within 14 days, they will be contacted via email, telephone or text message by service administrators, IAPT staff or Research Network Clinical Studies Officers to check whether they have received the letter and asking them if they wish to participate in the trial. In all cases, we will follow procedures that are in line with the policy of the respective trust as covered in the GDPR statement signed by each patient and will respect any opt outs that the trust may have received via national or other routes.

Patients who are potentially interested in taking part will be contacted by the researchers for an initial screening to confirm the presence of symptoms and history of high-intensity treatment for depression, and to provide further information on the research. If positive on the screen, potential participants will be invited to take part in a structured clinical interview conducted via videoconferencing to confirm eligibility and, if eligible, to complete baseline assessments by completing web-based questionnaires. Clinical interviews will be conducted as soon as possible after initial contact and screening, while baseline questionnaire assessments will take place within a window of 4 weeks before randomisation. The invitation for this assessment will include the patient information sheet (PIS) and informed consent will be taken before the start of the assessment by asking participants to sign and return the consent form electronically. Eligible, fully informed and consenting participants will then be entered into the study and randomisation (see Fig. 2).

**Fig. 2 Fig2:**
[figure not shown]
CONSORT diagram describing flow of participants through the study

## Assignment of interventions: allocation

### Sequence generation {16a}

We will allocate individual participants to either MBCT or TAU at a ratio of 1:1 through remote randomisation at the UKCRC-registered Exeter Clinical Trials Unit (ExeCTU), following informed consent, completion of baseline assessment and enrolment in the trial. Randomisation will use minimisation on depression severity (PHQ-9 < 19 versus ≥ 19), antidepressant use at baseline and recruitment site. Use of a validated password website will ensure concealment. Participants will be informed of their allocation by an unblinded member of the research team.

### Concealment mechanism {16b}

Use of a validated password website will ensure concealment.

### Implementation {16c}

Participants will be informed of their allocation by a member of the research team.

## Assignment of interventions: blinding

### Who will be blinded {17a}

As baseline assessment of participants is carried out prior to randomisation, there is no risk of disclosure of treatment allocation to the assessor at the time. Use of remote assessments, initiated through automated email, will rule out any potential effects of assessors on assessments of outcomes at 10-week and 34-week follow-ups. The statistician analysing outcome data will remain blind to treatment allocation throughout the analysis, which will be conducted with groups indicated by an anonymised code. The senior statistician will be unblinded throughout.

### Procedure for unblinding if needed {17b}

In the unlikely event that a participant has an adverse reaction within either treatment arm, unblinding may be necessary. We will unblind researchers only when knowledge of the treatment arm is deemed essential to the management of the patient by their GP. Any unblinding will be recorded, although we do not expect any biasing influences on follow-up assessments given that these are conducted remotely and without direct contact with the researchers.

## Data collection and management

### Plans for assessment and collection of outcomes {18a}

At baseline, trained research assistants will administer clinical interviews via videoconferencing and ask participants to complete web-based self-report questionnaires via secure online portal. We will use the Mini-International Neuropsychiatric Interview (MINI) [21] to assess eligibility. Post-treatment and follow-up assessments will consist of questionnaires only and in line with procedures at baseline will be conducted remotely by asking participants to complete self-report questionnaires on a dedicated webpage via secure online portal. Self-report questionnaires will include the Patient Health Questionnaire 9 (PHQ-9, [20]) to assess the severity of depressive symptoms, the Generalized Anxiety Disorder Questionnaire 7 (GAD-7, [24]) to assess severity of anxiety symptoms [24], the Phobia Scale to assess symptoms of phobia, the Work and Social Adjustment Scale to assess general levels of adjustment, the Warwick-Edinburgh Mental Wellbeing Scale (WEMWBS, [25]) to assess emotional well-being, the Experiences Questionnaire Decentering Scale [26] and the Five Factor Mindfulness Questionnaire [27] to assess candidate processes of action. Health economic analyses will use the EQ-5D [32] as a generic measure of health status and a self-report version of the Adults Service Use Schedule (AD-SUS) to assess health service use [19].

### Plans to promote participant retention and complete follow-up {18b}

Use of remote assessments will reduce burden on participants and serve to promote retention.

### Data management {19}

Randomisation, data management and quality assurance will be undertaken by ExeCTU under the supervision of the CI, senior trial statistician and quality assurance manager. Routine clinical notes will be stored according to standard practice within the NHS services hosting the research. Recordings of the videoconferencing therapy sessions along with the automatically produced transcripts of the sessions will be stored on a secure server at the University of Surrey where they will be accessible to the lead scientists for purposes of therapist supervision and manual adherence checks. Data from the assessments will be entered by the research team on a secure, web-based system maintained by the ExeCTU. Data from online questionnaires will be quality checked by the research team. Consent forms will be stored separately from data and data will be anonymised wherever possible.

The datasets generated during and/or analysed during the trial will be stored in a non-publicly available repository at Sussex Partnership NHS Foundation Trust upon publication of main study results. Anonymised data may be accessed and analysed by members of the project team and by researchers collaborating with members of the project team on the analysis of these data. All personal identifiable data, with the exception of the consent form and the video recordings, will be destroyed as soon as the study closes, unless participants have consented to be contacted for future research, in which case we will keep their contact details for 5 years. Audio recordings of qualitative interviews will be destroyed immediately after transcription. Research data with personal information removed and replaced through a code and original research records, including video recordings of assessment interviews and therapy sessions, will be retained for 10 years, before being destroyed. The electronic records will be kept for 10 years after the end of the study. Publications will not contain any patient-identifiable information.

### Confidentiality {27}

Any information collected as part of the trial will be kept strictly confidential within the research team and the services involved. Both within the research team and the services confidentiality will be broken only in exceptional circumstances, if it is felt by the researcher or therapist that a patient or someone else is at immediate risk and the team will need to contact GPs or other relevant professionals.

All data will be stored and processed in line with General Data Protection Regulation (GDPR, 2018). Personal data will be link-anonymised and identified by a code known only to the research team. Names and contact details will be stored in password-protected files on secure servers and separately to link-anonymised data. In order to assess manual adherence and therapist competency, therapy sessions will be video recorded with the consent of all participants appearing in the recording. Access to these recordings and the transcripts of the sessions will be restricted to the research team and collaborating researchers. Recordings and anonymised transcripts will be stored on secure servers at the University of Surrey.

Direct quotations from qualitative interviews may be used; however, it will not be possible to identify the participant from these. Clinical records will be stored on secure servers with access restricted to the trial manager and clinical team.

### Plans for collection, laboratory evaluation and storage of biological specimens for genetic or molecular analysis in this trial/future use {33}

As described under 26b, there will be no biological specimens collected.

## Statistical methods

### Statistical methods for primary and secondary outcomes {20a}

All analyses will be carried out using an a priori statistical analysis plan as agreed with the TMG and TSC.

Participant characteristics at baseline (including number of previous depressive episodes and IAPT service) will be set out descriptively by the treatment arm. The primary analysis approach will use the intention-to-treat (ITT) principle (all participants will be included in the analysis according to their randomised allocation irrespective of the treatment actually received) including observed data only. All outcomes will be reported descriptively at baseline, and at 10 and 34 weeks’ follow-up. Continuous outcomes will be analysed using linear regression models. The binary outcome variables will be analysed using logistic regression. All analyses will adjust for participant covariates used in randomisation, with adjustment for baseline scores for continuous outcomes. We will assess other participant characteristics at baseline and will consider adjusting for any covariates that are found to be substantively unbalanced, should such covariates be considered predictive of outcome. Inferential between-group comparisons (MBCT vs TAU) for the primary and all secondary outcomes will be performed at 34-week follow-up. As a sensitivity analysis, we will perform a complier average causal effect (CACE) analysis for continuous outcomes only, to estimate the treatment effect while accounting for non-adherence to treatment. A participant in the intervention arm will be considered to be a ‘complier’, if a minimum of four treatment sessions were attended. Mixed effects regression models with a random effect on individual participant will be performed for continuous and binary outcomes, including participants with outcome data reported for at least one follow-up time. To address the potential for clustering effects by IAPT service, we will perform sensitivity analyses using mixed effects regression models for the primary and secondary (continuous and binary) outcomes, with a random effect on IAPT service. Similarly, to address the potential for effects of clustering by therapist, further sensitivity analyses will test for the effect of individual therapists or therapist seniority. Mixed effects model with a random effect on individual therapist will also be performed. As a further sensitivity analysis, therapist seniority will be added as a fixed effect within the primary model for the primary outcome and all secondary outcomes. To explore effects under conditions of different inclusion criteria, a sensitivity analysis will be run including only those patients who failed to meet both criteria for reliable recovery according to IAPT conventions, that is reliable change in symptoms and symptom levels below caseness. We will also perform a sensitivity analysis (primary outcome only) to include any data collected outside the 7-day window. Sensitivity analyses will be based on the ITT principle (except the CACE analysis). Should further sensitivity analyses be indicated, these will be described in the statistical analysis plan.

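### Logistic models for recovery-type and GAD-7-based outcomes omit the continuous baseline scores: the comparison stays valid, but a little power is given up needlessly

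*Protocol article*

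**What the plan says.** All of this is in the Protocol article.

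- Statistical methods {20a} sets the model for binary outcomes: "The binary outcome variables will be analysed using logistic regression". It then gives the covariate rule: "All analyses will adjust for participant covariates used in randomisation, with adjustment for baseline scores for continuous outcomes".
- Sequence generation {16a} lists the covariates to which that rule refers: "Randomisation will use minimisation on depression severity (PHQ-9 < 19 versus ≥ 19), antidepressant use at baseline and recruitment site". GAD-7 is not among them.
- Secondary outcomes defines the binary endpoints: "A series of binarised outcomes will be derived, based on PHQ-9 and/or GAD-7". The first group is described as follows: "Recovery, reliable recovery, and reliable improvement will be reported using (i) PHQ-9 only to align with depression research literature". The same three are also defined on PHQ-9 and GAD-7 together. Then: "We will also report deterioration and reliable deterioration with regard to PHQ-9 and GAD-7 separately".
- Statistical methods {20a} leaves one further route open. For other baseline characteristics the team "will consider adjusting for any covariates that are found to be substantively unbalanced, should such covariates be considered predictive of outcome".
- Plans for assessment {18a} confirms that PHQ-9 and GAD-7 are both completed at baseline.

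The article gives no reason for treating binary and continuous outcomes differently.

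**The concern.** The entry floor for PHQ-9 is 10 (Eligibility {10}), which is also the caseness threshold, so recovery means falling below the entry floor. A participant who enters at 10 needs a fall of 10 − 9 = 1 point. One who enters at 18 needs 18 − 9 = 9 points. Both lie below the split at 19, so the logistic model treats their baseline severity as the same. Baseline GAD-7 is neither an entry criterion nor a minimisation factor, so it can vary freely between participants and, by chance, between arms. It still helps to decide who counts as recovered on the combined definition, which is the one aligned with IAPT practice.

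At stake is some precision on secondary outcomes that IAPT services are likely to read. The protocol states a rule here, so an analysis plan that follows it would leave the scores out, and one that adds them would depart from the published rule.

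**Working it through.** **1. The protocol's own figure.** Sample size {14} gives a difference of 2.59, SD 5.4, 90% power and alpha 0.05 (taken as two-sided, which is not stated). The normal formula is n per arm = 2(1.960 + 1.282)² × 5.4² / 2.59² = 91.4, rounded up to 92, or 184 in total. The t-test version gives 92.3, rounded up to 93, or 186 in total, as stated. With 20% attrition, 93 / 0.8 = 116.25, rounded up to 117 per arm, or 234. The sample size reproduces. It concerns the primary outcome only.

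**2. The two models compared.**
- As written: logit P(outcome) = intercept + arm + [PHQ-9 ≥ 19] + antidepressant use + site (two terms).
- With the change: the same, plus the continuous baseline score or scores.

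Both were fitted to simulated trials of 186 participants allocated 1:1, with a two-sided Wald test at 0.05.

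**3. Assumptions not in the document.**
- Baseline-to-follow-up correlation r from 0.3 to 0.6.
- Baseline PHQ-9 limited to 10 to 27, mean about 17, SD 4.2.
- TAU follow-up mean 13.
- GAD-7 effect 0.8 × 2.59 = about 2.1.
- 70% on antidepressants.
- GAD-7 cut-off 8; reliable change of 6 on PHQ-9 and 4 on GAD-7.
- For the combined and GAD-7 outcomes, a PHQ-9 to GAD-7 correlation of 0.6.

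The follow-up SD (5.4) and the effect (2.59) are taken from Sample size {14}. Recovery was then about 26% under TAU and 44% under MBCT.

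**4. PHQ-9 outcomes (4,000 trials per row), power without and then with the continuous score.**

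| r | Recovery (< 10) | Gain | Fall of ≥ 6 points | Gain |
|---|---|---|---|---|
| 0.3 | 72.3% to 72.8% | 0.5 | 73.1% to 75.1% | 2.0 |
| 0.4 | 73.8% to 75.4% | 1.6 | 77.6% to 78.0% | 0.4 |
| 0.5 | 75.1% to 77.7% | 2.6 | 83.0% to 83.4% | 0.4 |
| 0.6 | 77.4% to 80.7% | 3.3 | 89.4% to 89.2% | −0.2 |

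Simulation error is about 0.7 points per power figure, so the recovery gain at r = 0.3 is not distinguishable from nil. The gains are small because the split at 19 correlates 0.82 with the continuous score, so 0.82² = 67% of its linear variation is already in the model. With a mean baseline of 18.2 and r = 0.5, recovery goes from 71.6% to 73.4%.

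**5. Outcomes that use GAD-7 (2,000 trials per row).**

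| r | Combined recovery, adding both scores | Gain | GAD-7 rise of ≥ 4, adding baseline GAD-7 | Gain |
|---|---|---|---|---|
| 0.3 | 66.0% to 66.3% | 0.3 | 26.6% to 30.6% | 4.0 |
| 0.5 | 62.8% to 65.6% | 2.8 | 21.6% to 22.2% | 0.6 |
| 0.6 | 67.2% to 71.2% | 4.0 | 11.6% to 12.6% | 1.0 |

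**6. Separate check.** A further simulation (n = 186, 2,000 trials, assumed correlations 0.3 to 0.6) gave gains of about 0 to 4 points for PHQ-9 recovery, 2 to 6 for combined recovery, 1 to 5 for any GAD-7 rise and 0 to 2 for PHQ-9 improvement of 6 or more. Taken with the tables, the range for combined recovery is 0 to 6.

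**7. Rare outcomes.** Under the same kind of assumptions, a PHQ-9 rise of 6 or more occurred in 1 to 4% under TAU, which is 0.01 × 93 = 0.9 to 0.04 × 93 = 3.7 participants, and in fewer under MBCT. The model as written already failed to converge in over 85% of those runs.

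**The case against.** The case for leaving the rule alone has several parts.

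- **Validity.** Omitting a prognostic covariate does not invalidate a randomised comparison. A reader might infer that the binary results would be biased or the trial weakened overall. The documents do not support that: the primary outcome and the continuous GAD-7 analysis both adjust for their baseline scores, and no power is claimed for any binary outcome. This stands.
- **Size for GAD-7.** A reader might infer a larger loss from a GAD-7-only recovery outcome. For a stand-in of GAD-7 < 8 alone, power moves from 62.5% to 67.0% at r = 0.4 and from 65.8% to 73.0% at r = 0.6. Secondary outcomes defines no such endpoint. GAD-7 stands alone only for deterioration, and in combined recovery the PHQ-9 condition and the split already carry part of the information. This stands, and those figures should not be used.
- **Change-based outcomes.** Reliable improvement contains the baseline score in its definition, and the simulated gain on PHQ-9 is close to nil. It would be wrong to say that all binary outcomes suffer alike. This stands.
- **Imbalance.** Chance GAD-7 imbalance is not wholly without remedy, because the clause on unbalanced predictive covariates could bring baseline GAD-7 in. It stands only in part: the clause is discretionary, is triggered by the observed data, and yields no precision when the arms happen to be balanced.
- **Estimand.** Adding a covariate to a logistic model changes the conditional odds ratio being estimated. This stands, and a marginal summary answers it.
- **The analysis plan.** It is not shown and could add the scores. The point nevertheless concerns a stated rule, not an omission.

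**Conclusion.** The point holds as a low-cost improvement to secondary analyses. As written, the logistic models for recovery-type outcomes omit continuous baseline PHQ-9, and those for outcomes that use GAD-7 omit any baseline GAD-7, although both are collected. The power given up is about 0 to 4 percentage points for PHQ-9 recovery, 0 to 6 for combined recovery, and close to nil for PHQ-9 improvement.

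These sizes depend on the assumed correlations of 0.3 to 0.6 and on assumed GAD-7 cut-offs and distributions, none of which the protocol gives. At r = 0.7 the gain for PHQ-9 recovery would be 85.8 − 79.0 = 6.8 points. The reading of the covariate rule rests on the text alone and needs no assumption.

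**What to change.** Amend the covariate sentence in Statistical methods {20a}, before any unblinded analysis, so that in addition to the minimisation factors:

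- the logistic models for recovery, reliable recovery and reliable improvement include continuous baseline PHQ-9, and also baseline GAD-7 where the outcome is defined on both scales;
- the models for GAD-7 deterioration include baseline GAD-7 where event numbers support it, with that condition set in advance.

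Do not extend this to every binary model: PHQ-9 deterioration may have too few events even for the covariates already planned.

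The cost is one clause. It needs no new data and changes neither the sample size nor the primary analysis. The one drawback is that the odds ratio becomes conditional on the baseline score, so report a standardised risk difference beside it.
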